### Washout Period

The purpose of the 21-day washout period is to mitigate or minimize any potential carryover effects from the intervention. The term *carryover effect* refers to the persistence of the previous intervention’s effect or the impact of the initial intervention that extends beyond its duration and influences the subsequent intervention’s effect. By incorporating a washout period, we aim to ensure a clearer distinction between the effects of each intervention and minimize any potential interference or bias [24].

The available evidence on determining the appropriate washout period to eliminate the carryover effect effectively is limited. The conventional approach for determining the washout period is often based on the concept of 5 half-lives of the specific drug involved [25]. To address the carryover effect in this study, we used 2 strategies. First, we implemented a washout period of 21 days between interventions. This time gap was intended to allow for a sufficient delay to minimize the memory of the previous intervention and any lingering effects from the previous intervention. In addition, for the second intervention, the investigators carefully selected a different topic from the assignment to ensure that students would not easily recall specific details from the previous intervention. Furthermore, the research team ensured that the assignment content for the second intervention had similar complexities and requirements to maintain consistency across the study.

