### Outcomes and Measurements

The outcome measures will be (1) the usability of the technological tools (ChatGPT or conventional) for completing the assignments (primary outcome), (2) the participants’ perception of these tools as support for learning, and (3) the learning outcomes (secondary outcomes). Outcomes and measurements will be collected at 2 points: at the first follow-up, that is, after the first intervention (experimental or control) in the initial phase, and at the second follow-up, that is, after the second intervention (experimental or control) in the final phase (Figure 1).

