**Primary**				
	Usability (SUS^a^)	Continuous, nominal, ordinal, and 5-point Likert-type scale^b^	0-100 (SUS score: >68=above average and <68=below average) The individual scores of the participants for each question are transformed into a new number, which is then aggregated and multiplied by 2.5 to convert the initial range of scores from 0-40 to a new range of 0-100.	The frequencies, means, and SD of each item of the SUS scale will be calculated and compared using the McNemar or chi-square and Wilcoxon tests, respectively. In addition, each group’s usability scores and grades will be correlated using Spearman correlation.

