#### Perception of Ethics and Accountability

After the intervention with ChatGPT, the students will be asked to fill out a web-based survey about their perception of their AI experience. The survey will use multiple-choice questions, short open questions and a 5-point Likert scale, using closed-ended response options. This response format ensures enhanced objectivity and enables appropriate discrimination to address the research objectives effectively. A closed-ended Likert scale also promotes the participants’ comprehension and active engagement with the study. The questionnaire consists of four sections: (1) a sociodemographic information; (2) AI literacy exploration of positive learning experiences with AI; (3) an examination of negative experiences associated with AI use; and (4) an assessment of the potential for discussing accountability, fostering student leadership, and addressing ethical and equity concerns pertaining to the use of AI. One question of this survey was taken from a Swedish questionnaire about the use and views among university students about chatbots and other AI for learning. Qualtrics software will be used for survey design and data collection, as this software passed a security assessment of Carleton University, and its server is located in Montreal, Quebec, Canada.

The SUS survey is expected to take approximately 2 minutes to complete, whereas the perception survey is anticipated to be completed in approximately 10 minutes. By collecting data at multiple points in the study (2 points), we can evaluate the effects of each intervention and any potential carryover effects during the crossover period. In addition, it provides an opportunity to measure changes in outcomes within individual participants as they switch from one intervention to another.

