### Data Analysis

This study aims to compare the 2 interventions in terms of usability, student perception, and learning outcomes. The crossover design allows for within-group and between-group comparisons, enabling a comprehensive analysis of students’ perceptions of the use of the intervention and its impact on their learning, as well as the effects of the intervention on their learning outcomes.

The use of an identification code will anonymize data. The data set will be exported from the datasheet and imported into the SPSS software (version 28.0; IBM Corp) for Mac, where the data will be subjected to analysis with a confidence level of 95%. Descriptive statistics, including the calculation of frequencies, will be performed on the sociodemographic variables of the students. The usability scale and grades at each assessment time will be summarized using mean and SD. The nonparametric Wilcoxon test will be used to compare the differences between these variables.

The frequencies, means, and SDs of each item of the SUS scale will be calculated and compared using the McNemar or chi-square and Wilcoxon tests, respectively. In addition, the usability scores and the grades of each group will be correlated using Spearman correlation.

For the analysis of perception and usability outcomes, we will use the Spearman correlation coefficient to assess the relationship between the 2 scales. This statistical approach was chosen to measure the strength and direction of the associations between variables when the data may not conform to a linear pattern. Using the Spearman correlation coefficient, we aim to better understand how perceptions and usability factors are interrelated, providing a robust basis for our research findings and conclusions. To assess the internal consistency of the scales, Cronbach α coefficient will be calculated for both constructs and for each individual item.

To categorize the students into groups of low and high performance (using a cut-off value of 80) and classify the SUS scale into high and low usability groups (with a cut-off value of 50), appropriate statistical tests will be applied. Specifically, Fisher exact test or Pearson chi-square test will investigate the associations between the categorized scales and sociodemographic characteristics.

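### The only score-level test for SUS and grades is a Wilcoxon test that ignores period and sequence and is not clearly indexed by tool

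*Protocol article*

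**What the plan says.** The Data Analysis section opens with a tool-against-tool aim: "This study aims to compare the 2 interventions in terms of usability, student perception, and learning outcomes". It then describes the data by time, "The usability scale and grades at each assessment time will be summarized using mean and SD", and the next sentence gives the test: "The nonparametric Wilcoxon test will be used to compare the differences between these variables". It does not say whether this is the signed-rank or the rank-sum test, or how the pairs are formed.

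For the primary outcome, Table 1 adds comparisons of the individual SUS items, "calculated and compared using the McNemar or chi-square and Wilcoxon tests, respectively". For grades it lists only mean and SD. No section names a period or sequence term, or a comparison of sequence AB with sequence BA.

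Three other statements bear on this:

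- Outcomes and Measurements: "Outcomes and measurements will be collected at 2 points", one after each period. At each point one sequence has just used ChatGPT and the other conventional tools.
- Washout Period: "for the second intervention, the investigators carefully selected a different topic from the assignment", with the assurance that "the assignment content for the second intervention had similar complexities and requirements to maintain consistency across the study".
- Perception of Ethics and Accountability, on having two time points: "we can evaluate the effects of each intervention and any potential carryover effects during the crossover period".

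**The concern.** In an AB/BA crossover each student's two scores differ by tool and by period. Here period also carries the assignment topic, because everyone changes topic at the crossover. A test that does not separate the two has one of two problems, depending on how the pairs are formed.

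- If the pairs are time 1 versus time 2, as the order of the sentences allows, the tool effect has opposite signs in the two sequences and cancels at 1:1.
- If the pairs are ChatGPT versus conventional, the tool effect is kept. The period effect then has opposite signs in the two sequences. It inflates the spread and, when the sequences are unequal, shifts the estimate.

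This comparison carries the primary outcome, and the Results section intends to use the resulting effect sizes to plan larger trials. The carryover remark also promises more than two post-period scores can separate.

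**Working it through.** **Inputs.** From the article: 1:1 allocation to AB or BA; two post-period measurements; 45 evaluable students and 50 recruited (Sample Size). The article gives no SD for SUS or grades, no expected tool difference and no period effect, so there is no figure of the plan's own to reproduce for this comparison. Assumed: normal errors, two-sided alpha 0.05, no carryover, and all effects in units of the SD of the within-student difference (SD = 1).

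**Algebra.** Let τ be the tool effect (ChatGPT minus conventional) and δ the period effect (period 1 minus period 2). The expected within-student values are:

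| | ChatGPT − conventional | Period 1 − period 2 |
|---|---|---|
| AB | τ + δ | τ + δ |
| BA | τ − δ | −τ + δ |

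- Time-wise pairs, pooled mean: δ + τ(nAB − nBA)/n. At 1:1 this is δ alone.
- Tool-wise pairs, pooled mean: τ + δ(nAB − nBA)/n. Pooled variance: 1 + δ²[1 − ((nAB − nBA)/n)²].
- Period-adjusted: (period 1 − period 2 in AB) − (period 1 − period 2 in BA) = 2τ. The period effect drops out whatever the split.

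**Tool-wise reading, balanced sequences (23/22), τ = 0.5.** The pooled SD rises to √1.25 = 1.12 at δ = 0.5 and √1.5625 = 1.25 at δ = 0.75. The standardised effect therefore falls from 0.50 to 0.5/1.12 = 0.45 and 0.5/1.25 = 0.40. Simulated power:

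| δ | Signed-rank by tool, period ignored | Rank-sum of period differences, AB vs BA |
|---|---|---|
| 0 | about 89% | about 89% |
| 0.5 | about 85% | about 89% |
| 0.75 | about 78% | about 89% |

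A separate run on a points scale gives the same pattern (25/25, SD of the difference 14.1, tool effect 7 points). Power is 92%, 89%, 81% and 66% at period effects of 0, 5, 10 and 15 points, against 90% to 92% adjusted.

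**Tool-wise reading, unequal sequences, τ = 0, δ = 0.5.**

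- 27/18: shift 0.5 × 9/45 = 0.10 SD; type I error about 7%.
- 30/15: shift 0.5 × 15/45 = 0.17 SD; type I error about 15%.
- Period-adjusted test: about 5% at both splits.

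These errors are conditional on the split. Under simple randomisation of 45, a split of 30/15 or worse has probability 2 × P(X ≤ 15) = 3.6%, with X binomial(45, 0.5). Averaged over all splits, type I error at δ = 0.5 is close to 5%, while power at τ = 0.5 is about 81%.

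**Carryover.** Two sequences and two periods give four cell means. After the overall mean, the tool effect and the period effect, one contrast is left: student totals in AB against BA. Any carryover difference, any sequence-group difference and any tool-by-period (here tool-by-topic) interaction all fall into it. It is also weak: with 22 and 23 students, 80% power needs about 2.80 × √(1/22 + 1/23) = 0.84 SD of the totals, or about 0.85 with t quantiles.

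**The case against.** **A reader might infer that the planned test has no power for the trial's question.** On the time-wise reading that would be so: a 0.5 SD tool effect is detected about 3% of the time, and a pure 0.5 SD period effect is declared significant about 89% of the time. But the time wording belongs to the sentence on descriptive summaries. The Study Hypotheses, the Usability section and the opening of Data Analysis all frame the comparison by tool. The sentence is ambiguous, so the documents do not support resting the point on those figures. What stands is that the wording permits the wrong contrast and should not.

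**A reader might infer a systematically inflated false-positive rate.** The documents do not support that either. Under simple randomisation the period term is a random plus or minus for each student, and the unconditional error stays near 5%. With balanced sequences the test is conservative. Inflation needs a realised imbalance or sequence-related loss, and nothing in the article points to the latter.

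**A reader might infer that carryover cannot be examined at all.** A test exists; it is weak, and its result cannot be attributed to carryover alone.

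**The period effect may be small.** The article asserts that the two assignments are comparable, and topic difficulty may matter more for grades than for perceived usability. This is fair. The assertion comes without data, and adjustment costs almost nothing if it proves right.

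**An article condenses, and a fuller plan may exist.** That limits the point to what is printed. But the article does name the test, and a plain Wilcoxon test is less suited to this design than the adjusted version.

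**Conclusion.** The point holds as a should-fix. The stated score-level test does not make clear that it contrasts tools, and it ignores period and sequence in a design where topic changes with period. On the plausible tool-wise reading with balanced sequences, the harm is lost power: about 4 percentage points at a period effect of 0.5 SD and about 11 at 0.75 SD, for a tool effect of 0.5 SD and 45 completers. With a realised imbalance there is also a shift of δ(nAB − nBA)/n. All of these sizes rest on assumed effects, because the article gives no SD, tool effect or period effect. The direction does not depend on them: the period-adjusted comparison removes the period effect at any split. The carryover sentence claims more than the design can isolate.

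**What to change.** 1. In Data Analysis, define the contrast as ChatGPT versus conventional tools within student, for the total SUS score and separately for grades.
2. Adjust for period, in one of two ways:
   - a rank-sum test comparing period 1 minus period 2 differences between AB and BA, with a Hodges-Lehmann estimate and 95% CI. The between-sequence shift is twice the tool effect, so halve it for reporting; or
   - a mixed model with tool, period and sequence as fixed effects and student as random, reporting the tool difference with 95% CI.
3. In Perception of Ethics and Accountability, say that with two post-period measurements carryover is aliased with sequence and with tool-by-period (topic) interaction and cannot be separated from them. Do not make the primary analysis conditional on a carryover test.

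The cost is analysis wording and about one degree of freedom; no new data are needed. The article reports that data collection took place in October and November 2023, so the change should be recorded before scores are compared by tool. Coded sequence labels are enough to run the rank-sum test while the analysts stay blinded.

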### Intervention and Measurement

During the initial phase of the study, participants assigned to sequence AB will use ChatGPT (experimental intervention: group A) to complete their assignments, while participants assigned to sequence BA will use conventional web-based tools (control intervention: group B) and serve as a control group. In the subsequent period, the interventions will switch between the 2 groups. Students will not know which one is the “intervention of interest” and which one will be the “comparator.” As mentioned above, the learning activity to be assessed in this project is part of the mandatory course activities. This means that all students will receive a grade for this assignment. Therefore, the instructor will not be able to determine which students have or have not participated in the study. Students’ acceptance to participate in this study only gives permission to the research team to use their data for research purposes, but all students will be assessed for this work as part of the course. The course instructor will not be responsible for grading the assignments associated with the intervention. The TA will be responsible for grading assignments and assigning a unique number code to each participating student, which will be linked to their names. This coded information will be sent to the RA to preserve anonymity throughout the process. The RA will receive the graded assignments, the student names, and their respective codes from the TA. The RA will collect the grades of the student participants and submit them to the research team members responsible for the analysis. It is important to note that the research team, which includes the course instructor, will not have access to the participants’ names. Only the grades and the participant codes will be accessible for analysis. The research team, including the course instructor, will perform the data analysis based solely on the provided grades and participant codes, without access to any identifiable information. This further ensures that anonymity is strictly maintained throughout the analysis phase.

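### The perception–usability correlation has no sequence term, although the AI perception survey and the ChatGPT-period SUS are taken in a period and on a topic fixed by sequence

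*Protocol article*

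**What the plan says.** Under Data Analysis, the protocol article plans a single coefficient for this question: "For the analysis of perception and usability outcomes, we will use the Spearman correlation coefficient to assess the relationship between the 2 scales". No sequence or period term is mentioned, and the SUS score to be used (ChatGPT, conventional tools or both) is not named.

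Three other sections fix when the measurements are taken:

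- **Perception of Ethics and Accountability:** this section ties the AI survey to the ChatGPT task: "After the intervention with ChatGPT, the students will be asked to fill out a web-based survey about their perception of their AI experience".
- **Intervention and Measurement:** in the first period "participants assigned to sequence AB will use ChatGPT" while BA students use conventional tools. Then "In the subsequent period, the interventions will switch between the 2 groups".
- **Washout Period:** "we implemented a washout period of 21 days between interventions", and "for the second intervention, the investigators carefully selected a different topic from the assignment". The same section says that the second assignment "had similar complexities and requirements to maintain consistency across the study".

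**The concern.** In a crossover, each student gives one measurement per tool, and the tool comparison is made within students. A correlation between two measurements that both belong to the ChatGPT condition does not have this protection. Each student contributes one pair, and the sequence decides the period, the topic and whether the student has already done a conventional-tool assignment in the trial.

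Suppose one of these features moves perception and the SUS in the same direction. A pooled coefficient then shows an association even if, within each sequence, the two scales are unrelated. If they move in opposite directions, a real association is partly hidden. The article intends to draw conclusions from this coefficient on how perception and usability are interrelated, so the reader will take it as a student-level association.

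**Working it through.** **Timing from the text.** Each assignment has a 6-day window (Experimental Intervention, Control Intervention) and the washout is 21 days. If the washout starts when the first window closes, the ChatGPT task ends on day 6 for AB and on day 6 + 21 + 6 = 33 for BA. That is 27 days later, or about four weeks.

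| | AB | BA |
|---|---|---|
| Period of ChatGPT use, its SUS and the AI perception survey | 1 | 2 |
| Assignment topic | first | second |
| Conventional-tool assignment already done in the trial | no | yes |

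**The plan's own figure.** None is given for this correlation. The only design figure is 45 students, raised to 50 (Sample Size; 45/0.90 = 50). A two-sided 5% comparison of 84% with 50%, at 90% power with continuity correction, needs 44 per group, close to the stated 45. That figure concerns two proportions and supports no power statement here. I use n = 50, 25 per sequence, only as the number of pairs.

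**Formula.** Let rho be the correlation within each sequence, and d1 and d2 the BA minus AB shifts on the two scales in within-sequence SD units. With 1:1 allocation the pooled correlation is

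r = (rho + d1·d2/4) / √[(1 + d1²/4)(1 + d2²/4)].

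Neither rho nor the shifts are in the documents. All values below are assumptions.

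With rho = 0:

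- 0.5 SD on one scale only: numerator 0, so r = 0.
- 0.2 SD on both: 0.01/1.01 = 0.01.
- 0.5 SD on both: 0.0625/1.0625 = 0.06.
- 0.8 SD on both: 0.16/1.16 = 0.14.
- 1.0 SD on both: 0.25/1.25 = 0.20.

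With rho = 0.3:

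- 0.5 SD on one scale only: 0.3/√1.0625 = 0.29.
- 0.5 SD, same direction: 0.3625/1.0625 = 0.34.
- 0.5 SD, opposite directions: 0.2375/1.0625 = 0.22.
- 0.8 SD, opposite directions: 0.14/1.16 = 0.12.

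For scale, the standard error of a correlation near 0 with 50 pairs is about 1/√49 = 0.14.

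**Simulation.** Normal scores, 20,000 trials per setting, n = 50, two-sided 5% test, rho = 0:

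| Shift on the two scales (SD) | Pooled Spearman: mean | Pooled: rejects | Within-sequence ranks: rejects |
|---|---|---|---|
| 0 / 0 | 0.00 | 4.9% | 4.8% |
| 0.2 / 0.2 | 0.01 | 5.1% | 4.9% |
| 0.5 / 0 | 0.00 | 5.2% | 5.0% |
| 0.5 / 0.5 | 0.06 | 6.9% | 4.8% |
| 0.8 / 0.8 | 0.14 | 16.5% | 5.2% |
| 1.0 / 1.0 | 0.20 | 29.1% | 5.0% |

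With 44 pairs the 0.5, 0.8 and 1.0 rows reject in 6.8%, 14.7% and 26.5% of trials.

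**Cost of adjusting when there is no shift.** Ranking within each sequence lowers power at rho = 0.3 from 52.0% to 49.6%, a loss of 2.4 points. Ranking all students together and then removing the sequence means (partial Spearman) lowers it at rho = 0.4 from 79% to 78%, about 1 point.

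**The case against.** The strongest reply is that pooling is inferred from silence. The article does not say that the sequences are combined without adjustment, and stratifying a secondary correlation is often left to an analysis plan, which is not shown here. This stands in part. One coefficient for two scales is most naturally read as pooled, but it is not an express statement, and neither is the pairing with the ChatGPT-period SUS.

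A reader might also infer that perception is collected once per student. That is clear only for the AI survey under Perception of Ethics and Accountability. Outcomes and Measurements lists perception of both tools among outcomes collected at two points, and Usability has control participants complete a parallel survey about conventional tools. The point does not depend on this: even with two perception surveys, each tool's ratings would be tied to period and topic by sequence.

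The size is also open to challenge. No shift is documented. The second assignment was chosen to be comparable, and a survey on AI literacy, ethics and accountability may hardly react to the topic. That is fair for topic, but does not cover calendar time or having just used the comparator. The simulation further assumes one normal perception score, whereas the article describes mixed items in four sections and gives no total score. The percentages are therefore illustrative.

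Finally, the correlation across students in both orders is a legitimate descriptive quantity. That holds, provided it is not read as the association at a fixed period and topic.

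**Conclusion.** The point holds as a minor one. The time, topic and prior in-trial comparator use behind the AI perception survey and the ChatGPT-period SUS are fixed by sequence, and the stated correlation has no sequence term. A pooled coefficient can therefore carry a sequence component.

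This matters only if both scales shift. At an assumed 0.5 SD on both, the coefficient moves by 0.06 from zero, less than half its standard error. It becomes material at an assumed 0.8 to 1.0 SD on both.

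Three stronger readings are not supported:

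- **That the planned correlation is distorted.** The documents give no evidence of a shift, so the most that can be said is that it can be.
- **That the Fisher and chi-square tests share the fault.** They relate the categorised scales to sociodemographic characteristics, which are independent of a randomised sequence by design. A sequence shift cannot systematically create such an association.
- **That the primary SUS comparison is affected.** This point does not touch it.

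**What to change.** Under Data Analysis, name the ChatGPT-period SUS as the score paired with AI perception. Report the rank correlation partialled on sequence (AB/BA) with a 95% interval. In the perception row of Table 1, add that responses are shown by sequence as well as overall.

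The article reports that data collection took place in October and November 2023, so the remedy has to be in the analysis. Sequence is the randomised factor and is already recorded, so no new data are needed. The cost is a few lines of wording and, if there is no shift, about 1 to 2.5 points of power depending on how the ranks are formed.

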#### Usability

Participants in the experimental intervention (AI-ChatGPT intervention) will also be asked to fill out a survey regarding their perception of using generative AI as an assistance tool to complete their assignments. This survey aims to gather insights into their thoughts, opinions, and attitudes toward using AI in their learning experiences. Participants will have the opportunity to share their feedback on the effectiveness, benefits, challenges, and overall satisfaction while using AI for assignment completion. Their responses will provide valuable information on AI technology’s perceived value and acceptance in enhancing their learning experience. Participants in the control intervention (conventional tools) will complete the same survey, but regarding the usability of the conventional tools.

The System Usability Scale (SUS) will assess the participants’ perceptions of usability. The SUS is a valid questionnaire [26] and will be administered at the end of the interventions and when participants cross over to the other assistance tool (AI-ChatGPT or conventional web-based tools without AI). The SUS is commonly used in numerous studies to assess the effectiveness and usability of new technologies, including in the education field [27-29]. A recent systematic review of home-based telerehabilitation software systems for remote supervision revealed that the SUS tool was the most frequently used measure or tool across the studies examined [28]. This scale has been translated into several languages, including the American Sign Language [30-32]. The SUS questionnaire was originally developed as a “quick and dirty” tool, with the goal of providing a fast and nonintrusive assessment experience for participants [26]. The SUS consists of 10 items formulated as affirmative statements, for which users indicate their level of agreement or disagreement on a 5-point Likert scale (1=strongly disagree; 5=strongly agree). For the odd answers (1, 3, and 5), we will subtract 1 from the score that the user answered; for the even answers (2 and 4), the score will be subtracted from 5. The values of the 10 questions will be added and multiplied by 2.5. The final score can range from 0 to 100. Internal consistency will be calculated using Cronbach α per item and overall. This scale allows for the assessment of outcomes and comparisons within and between the 2 interventions (Table 1).

**Table 1 table1:** Overview of outcome measures.

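### SUS and grades are tested against sociodemographic characteristics only after being split at 50 and 80, which costs power in a supporting analysis; the SUS cut-off of 50 is unexplained beside Table 1's benchmark of 68

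*Protocol article*

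**What the plan says.** The Usability section of the protocol article defines the SUS total: "The values of the 10 questions will be added and multiplied by 2.5", and "The final score can range from 0 to 100". Table 1 also gives grades a 0-100 range and lists them as continuous.

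Two SUS reference values follow.

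- Table 1, in the measure column for the primary outcome: "SUS score: >68=above average and <68=below average". No test is attached to it.
- Data Analysis: the team will "classify the SUS scale into high and low usability groups (with a cut-off value of 50". The same sentence will "categorize the students into groups of low and high performance (using a cut-off value of 80" for grades.

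The article gives no reason for 50 and does not relate it to 68. The split variables have one stated use: "Fisher exact test or Pearson chi-square test will investigate the associations between the categorized scales and sociodemographic characteristics". Table 1 gives the same tests in its row for perception of AI.

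Elsewhere in Data Analysis the SUS total and grades stay undivided. For the comparison of the two, "The nonparametric Wilcoxon test will be used to compare the differences between these variables", and Spearman correlation relates SUS to grades and to perception.

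**The concern.** There are two linked problems.

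The first is the analysis choice. Two scores on a 0-100 range are each cut into two classes before being related to sociodemographic characteristics, in a trial planned for about 45 evaluable students. No test of these associations on the full scores is described. A split discards the ordering within each class, and a split far from the centre of the data leaves one class nearly empty. A real association could then go undetected.

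The second is the choice of 50. A reader who has been given 68 in Table 1 as the dividing line around average will meet students in a high-usability group whose scores Table 1 calls below average, with nothing in the text to explain why.

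**Working it through.** The plan gives no figure for this analysis, so there is none to reproduce. The 45 evaluable students come from Sample Size and are taken as given; that calculation uses neither SUS cut-off. The article gives no SUS mean or SD, so both are assumed and varied below.

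**Step 1: scores that carry both labels.** Ten items scored 0 to 4 sum to 0-40; times 2.5, this gives 41 attainable totals in steps of 2.5. Those above 50 and below 68 are 52.5, 55, 57.5, 60, 62.5, 65 and 67.5, which is 7 of the 41.

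**Step 2: how many students that could be, and what a split keeps.** For a normal score with mean m and SD s:

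- share with both labels = Φ((68 − m)/s) − Φ((50 − m)/s)
- p = share below cut-off c = Φ((c − m)/s); expected number in the low class = 45p
- information kept by a split at c, relative to the full score = φ(q)² / [p(1 − p)], with q = (c − m)/s

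Worked example, m = 68, s = 15, c = 50: q = −18/15 = −1.2; p = 0.115; 45 × 0.115 = 5.2 students; φ(−1.2) = 0.194, so 0.194² / (0.115 × 0.885) = 0.37. Share with both labels = 0.500 − 0.115 = 0.385.

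| Mean | SD | Both labels | Low class at 50, of 45 | Kept at 50 | Kept at 68 |
|---|---|---|---|---|---|
| 60 | 12.5 | 0.527 | 9.5 | 0.50 | 0.55 |
| 60 | 15 | 0.451 | 11.4 | 0.54 | 0.57 |
| 60 | 20 | 0.347 | 13.9 | 0.58 | 0.60 |
| 68 | 12.5 | 0.425 | 3.4 | 0.29 | 0.64 |
| 68 | 15 | 0.385 | 5.2 | 0.37 | 0.64 |
| 68 | 20 | 0.316 | 8.3 | 0.47 | 0.64 |
| 75 | 12.5 | 0.265 | 1.0 | 0.13 | 0.57 |
| 75 | 15 | 0.273 | 2.2 | 0.22 | 0.59 |
| 75 | 20 | 0.258 | 4.8 | 0.35 | 0.61 |

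So about 26% to 53% of students would carry both labels, and the low class at 50 would hold about 1 to 14 of 45. A split at 50 keeps 13% to 58% of the information, and a split at 68 keeps 55% to 64%.

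**Step 3: power.** Simulation, 4,000 runs per row: two sociodemographic groups of 22 and 23 students, SD 15, true difference 0.8 SD (12 SUS points), scores rounded to steps of 2.5 and held within 0-100, a total of exactly 50 counted as high, test level 0.05.

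| Assumed mean | Wilcoxon rank-sum, full score | Fisher, cut 50 | Fisher, cut 68 |
|---|---|---|---|
| 60 | 0.73 | 0.45 | 0.44 |
| 68 | 0.72 | 0.30 | 0.50 |
| 75 | 0.73 | 0.09 | 0.49 |

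The full score has the highest power in every row. Moving the cut from 50 to 68 helps at means of 68 and 75 but not at 60, so changing the threshold alone does not recover the loss. No power was computed for grades split at 80. The same reasoning applies, but the size depends on where 80 falls among the grades, which the article does not say.

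**The case against.** Much of the case on the other side stands.

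- **The labels differ in kind.** Table 1's 68 is a benchmark against an average; 50 forms groups for one analysis. A score of 60 can lie below an average and above a grouping point without logical contradiction. A reader might infer that the reported share of students finding ChatGPT highly usable depends on which section is followed. The article does not support that: only Data Analysis defines high usability, and nowhere is that share an outcome.
- **No main result is touched.** A reader might also infer that the primary result is at risk. The comparison of the two tools uses Wilcoxon on undivided scores, the correlations use Spearman, and associations with sociodemographic characteristics appear in neither the objectives nor the hypotheses.
- **The power loss is conditional.** It would be too strong to say that a split at 50 always loses most of the power. At an assumed mean of 60, Fisher at 50 keeps 0.45 of a possible 0.73 and does no worse than a split at 68. Most of the power goes only at assumed means of about 68 or more.
- **Some details belong in an analysis plan.** Which class a total of exactly 50 joins, and whether the tables are run by tool, are points an article may leave to a fuller document. Neither is counted as a fault here, and the article does not say that both values from a student enter one test.

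What the objection does not answer is that 50 is unexplained beside 68, and that the only association tests described for SUS and grades against sociodemographic characteristics use the split scores, although the same section already uses rank methods on full scores.

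**Conclusion.** The point holds as a cheap improvement to a supporting analysis and as a request to reconcile two reference values. Splitting SUS at 50 lowers power for sociodemographic associations from about 0.72 to between 0.09 and 0.45, given 45 students in two near-equal groups, an SD of 15, a true difference of 0.8 SD and means of 60 to 75. All of these except the 45 are assumptions. That 52.5 to 67.5 falls on opposite sides of the two values follows from the article's own scoring and needs no assumption; the share of students affected does.

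**What to change.** In Data Analysis, replace the Fisher or chi-square tests of split SUS and split grades with tests on the undivided scores: Wilcoxon rank-sum for a characteristic with two categories, Kruskal-Wallis for more than two, and Spearman for an ordered or continuous one. Run them separately for ChatGPT and for conventional tools, so that each student enters a test once.

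Keep any high/low grouping for description only. Either use Table 1's 68 throughout, since the article ties that value to an average, or keep 50 with a stated reason and a sentence on how it relates to 68.

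The cost is a change of wording, with no new data and no effect on the sample size. What is given up is the high/low cross-tables as inferential results; they can still be shown as counts.
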